### Statistical analyses

Mixed modelling will be applied for longitudinal analyses of the data by using SPSS version 21. Mixed modelling can efficiently deal with missing data and unbalanced time-points [72]. This analysis will include two levels: the patients will constitute the upper level, and their repeated measures the lower level. First, for each outcome variable a saturated model will be postulated, with the primary or/and secondary outcomes as dependent variables. The saturated models will include treatment group, time, quadratic time, logarithm of time, and all treatment-time interactions as fixed effects. The deviance statistic [73] using restricted maximum likelihood [74] will be applied to determine the covariance structure. Next, the saturated fixed part of the models will be reduced by eliminating insignificant fixed effects using Wald tests, respecting that interaction effects must be nested under their main effects [75]. The significance of the difference between the saturated models and the parsimonious final models will be determined with the deviance statistic using ordinary maximum likelihood. The residuals of the model will be checked for normal distribution, which is necessary for a correctly fitted mixed model. Effect sizes will be calculated by dividing the differences between time-point and baseline estimations and the estimated baseline standard deviation. The definition of Cohen will be used for the interpretation of the effects sizes: an effect size of 0.20 is considered a small effect, 0.50 medium and 0.80 a large effect [76].

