### Intervention

The 1-year multidisciplinary lifestyle intervention aims at: 1) changing cognitions; 2) changing dietary habits; 3) encouraging and promoting physical activity; and 4) activating social support; and consists of twenty 2.5 h group sessions. The first 1.5-h of every group session is supervised by a mental health professional and a dietician. The last hour of each session is supervised by a physical therapist. Each lifestyle intervention group consists of a maximum of 10 patients to ensure that there is sufficient individual attention for every participant. Additionally, participants receive five individual counselling sessions of 45 min with a mental health professional, five individual sessions with a physical therapist and five with a dietician.

We developed the “PCOS lifestyle textbook” for participants, which describes the activities of each group session and the homework assignments. To standardize the treatment and to facilitate the therapist’s treatment adherence, we developed a therapist manual, which includes protocols for each session. The manual also includes PowerPoint slides to present at each group session.

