### Control group: usual care

Just like the lifestyle intervention group, the control group visits the hospital after the initial assessment during the 4 consecutive occasions at which they are similarly assessed as the CBT lifestyle intervention group. During these 5 measurement moments they have a short, unstructured consult with their treating physician. Participants in the control group are encouraged to lose weight through publicly available services (i.e. diets, visiting a dietician, going to the gym or participating in public programs such as Weight Watchers®) and use simple strategies, including self-monitoring of their diet. The physician also mentions the risk of overweight for both mother and child, and the relation between overweight and fertility. If patients fail to achieve their target weight during the 12-month study period (see below), they can participate in the lifestyle intervention, but are not included in the trial.

At the Erasmus MC, patients diagnosed with PCOS receive ovulation induction treatment when shifted to a lower BMI category. Meaning: 1) a weight loss of 4.0 BMI points; 2) a BMI < 34.0; and 3) weight loss maintenance over 3 months. The intervention group receives ovulation induction treatment after 1) a weight loss of 4.0 BMI points; 2) a BMI < 34.0; and 3) complying with the intervention group for more than 1 year.

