### Sample size calculation

The original sample size calculation in 2009 was based on an anticipated effect of a difference between the groups of 0.45 in terms of Cohen’s d in the primary outcome variable (BMI), with a power (1-beta) of 0.80 and an alpha level of 0.05 (two-sided) in a 2:1 ratio. This ratio was required for analysis of the secondary outcome: the effect of SMS within the intervention group. This resulted in 156 patients to be enrolled in the intervention group and 78 patients in the control group, a total of 234. This number was registered at the Dutch Trial Registry (TC 2450). On behalf of the Grant Foundation (MRace), an interim analysis was performed in May 2014. After inclusion of 150 patients, we applied an interim power analysis to the complete cases. The control group had a reduction from 33.3 ± 6.8 kg/m^2^ to 32.6 ± 6.6 kg/m^2^, an effect of Cohen’s d = 0.10, whereas the lifestyle intervention group showed a reduction from 33.8 ± 4.8 kg/m^2^ to 31.3 ± 5.1 kg/m^2^, an effect of d = 0.52 and a difference of 0.42. For the sample size calculation, we applied the method described by Aberson [71], with a power of 0.90, a two-sided alpha of 0.025 (corrected for the interim analysis) and five repeated measures linearly decreasing. We observed an intercorrelation of about 0.90 between all measurements. Maintaining a ratio of 2:1, the required sample is 84 participants in the lifestyle intervention and 42 in the control group, a total of 126 complete cases. With an observed drop-out proportion of 40%, a total of 210 participants are needed for the study. We anticipated to have a relatively high drop-out rate, because pregnancy leads to exclusion. Note that this sample size calculation is a conservative number, as it is based on a complete case analysis of variance. The intended multilevel analysis provides more power.

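### The primary mixed model has no therapy-group level although only the intervention is delivered in groups, so its standard error is understated if outcomes within a group are positively correlated

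*Protocol article*

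**What the plan says.** All references are to the protocol article.

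- **Statistical analyses.** The model is described as follows: "This analysis will include two levels: the patients will constitute the upper level, and their repeated measures the lower level". For the fixed part: "The saturated models will include treatment group, time, quadratic time, logarithm of time, and all treatment-time interactions as fixed effects". Neither part contains a term for therapy group.
- **Intervention.** The programme "consists of twenty 2.5 h group sessions", and "Each lifestyle intervention group consists of a maximum of 10 patients". Each woman also has individual sessions with the mental health professional, the physical therapist and the dietician, five of each.
- **Control group: usual care.** "Participants in the control group are encouraged to lose weight through publicly available services". No study therapy group is formed in this arm.
- **Sample size calculation.** The current target is 84 + 42 = 126 complete cases, raised to 210 for 40% drop-out, at a two-sided alpha of 0.025. The section adds: "Note that this sample size calculation is a conservative number, as it is based on a complete case analysis of variance", and expects the multilevel analysis to give more power. It contains no ICC and no design effect.

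**The concern.** Women in one therapy group share up to twenty sessions. Activating social support is a declared aim of the programme, and Table 2 includes a buddy system. Influence between members is therefore part of how the treatment is meant to work, and correlated weight trajectories within a group are plausible. Controls have no counterpart to this, so the extra variance would sit in one arm only.

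With the patient as the highest level, two different women are independent by construction. Choosing the covariance structure by deviance does not change that, because it concerns the repeated measures within one woman. The article specifies the hierarchy explicitly, so this is not a detail left to an unseen analysis plan. At stake are the width of the confidence interval and the p-value of the primary comparison.

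**Working it through.** **Inputs from the article.** Allocation 2:1; complete cases 84 and 42; maximum therapy-group size 10; drop-out 40%; two-sided alpha 0.025 (Sample size calculation).

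**Assumptions.** The ICC of the outcome within a therapy group is not given; 0.02 to 0.10 is used. Cluster size m is taken as 6 (10 less 40% drop-out) and as 10 (full groups). A mixed model also uses the earlier measurements of women who drop out, so for groups that start full the effective size lies between the two.

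**The plan's own figure.** 126 / (1 − 0.40) = 210. Drop-out is the only inflation applied.

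**Formulae.** Clustering acts in the intervention arm only.

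- Design effect: DE = 1 + (m − 1) × ICC
- SE ratio, true to modelled: √[(DE/84 + 1/42) / (1/84 + 1/42)] = √[(DE + 2)/3]
- True type I error at nominal 0.025: 2 × [1 − Φ(2.241 / SE ratio)]

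| m | ICC | DE | SE ratio | Type I error |
|---|---|---|---|---|
| 6 | 0.02 | 1.10 | 1.017 | 0.028 |
| 6 | 0.05 | 1.25 | 1.041 | 0.031 |
| 6 | 0.10 | 1.50 | 1.080 | 0.038 |
| 10 | 0.02 | 1.18 | 1.030 | 0.030 |
| 10 | 0.05 | 1.45 | 1.072 | 0.037 |
| 10 | 0.10 | 1.90 | 1.140 | 0.049 |

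The SE ratio depends on the 2:1 allocation, not on the totals, so the rows apply equally to 140 and 70 randomised women.

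**Check by simulation.** A two-sample test that ignores therapy group was run 20,000 times per setting. With 84 versus 42 and m = 6, type I error at nominal 0.025 was 0.028, 0.033 and 0.037 for ICC 0.02, 0.05 and 0.10. With 140 versus 70 and m = 10 it was 0.030, 0.037 and 0.049. These agree with the formula.

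**Does the stated power of 0.90 fail?** The interim means give a difference in BMI change of (33.8 − 31.3) − (33.3 − 32.6) = 1.8. The pooled baseline SD at 2:1 is √[(2 × 4.8² + 6.8²)/3] = 5.55. With correlation 0.90 the SD of change is 5.55 × √0.2 = 2.48. For 84 versus 42 at alpha 0.025:

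- SE without clustering: 2.48 × √(1/84 + 1/42) = 0.469, so power is Φ(1.8/0.469 − 2.241) = 0.945.
- With m = 6: 0.937, 0.926 and 0.905 at ICC 0.02, 0.05 and 0.10.
- With m = 10 and ICC 0.10: 0.87. This pairs full groups with the completer count of 84. Pairing full groups with all randomised women (140 versus 70) gives 0.98.

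On consistent inputs this test stays above 0.90 over the whole assumed range.

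**The case against.** The strongest reply has four parts.

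- **Size.** No ICC is given, and 10 is a maximum. At ICC 0.01 the standard error grows by only about 1% (1.008 with m = 6, 1.015 with m = 10). This stands, and the point has to be stated conditionally.
- **Standardisation.** A session-by-session therapist manual, common slides and fifteen individual sessions per woman should reduce variation between groups. The article does not say that therapists differ between groups; if one team leads them all, therapists add no between-group variance. This stands too, but influence between members remains.
- **Power.** A reader might infer that the stated power is missed, or that calling the sample size conservative is wrong. The documents do not support either reading. The reason given for that word concerns complete-case analysis and makes no claim about clustering. On matched inputs, power in the illustrative test stays at about 0.905 or more. The 126 could not be rebuilt with standard variants: a change-score test at d = 0.42 needs 66. Since the set-up of the cited method is not given, 126 is not called wrong. Even 66 inflated by the largest design effect, 66 × (1.90/2 + 1)/1.5 ≈ 86, stays below 126.
- **Estimability.** With 140 intervention women in groups of 10 there would be about 14 groups, or more if groups are smaller. A group variance may be estimated near zero, and a random slope may not converge. This calls for a fallback; it does not justify omitting the level.

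None of these supports treating members of one therapy group as independent.

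**Conclusion.** The point holds in conditional form. The stated model omits a level that the design has in the intervention arm only. For any positive within-group correlation, the standard error of the primary comparison is understated. For an assumed ICC of 0.02 to 0.10, the understatement corresponds to a true standard error about 2% to 8% larger with 6 completers per group, and up to 14% larger with full groups of 10. Type I error at nominal 0.025 is about 0.028 to 0.038, and at most about 0.049. The upper limit needs both full groups throughout and the largest assumed ICC.

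That the level is missing is certain; how much it matters is not. A reader might also carry the point over to the SMS comparison. That contrast is less affected if SMS was allocated within therapy groups, which the article does not state.

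**What to change.** Before the analysis, make these changes:

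- **Primary model.** Add a therapy-group random effect for intervention women only, with each control as her own cluster. Use a random intercept and, where estimable, a random time slope. Fall back to the intercept only if the model does not converge, and say so when reporting: an intercept that is constant over time largely cancels from change since baseline, so it protects the time-by-treatment effect less.
- **Inference.** Use small-sample degrees of freedom, and report the estimated ICC.
- **SMS comparison.** State whether SMS was allocated within or between therapy groups, and include the group term accordingly.
- **Sample size calculation.** Add one sentence that no allowance was made for therapy-group clustering. Nothing else there needs to change on this account.

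The cost is small: extra random-effect terms and a therapy-group identifier. The article does not say that the identifier is in the data set, but attendance at meetings is a listed outcome, so membership should be recoverable. The downsides are slightly wider intervals and possibly near-zero variance estimates with about 14 or more groups.

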### Randomisation

At the baseline, after the initial assessment, participants are randomized at a 2:1 ratio into the following groups: 1-year CBT lifestyle intervention with SMS (*n* = 78), 1-year CBT lifestyle intervention without SMS (*n* = 78), or the control group who receives usual care (*n* = 78) using a computer-generated random numbers table. A research nurse, who is not involved in the study, carries out the randomisation. Assignment is made by sequentially numbered, identical, sealed envelopes, each containing a letter designating the allocation (i.e. “A” for intervention with SMS, “B” for intervention without SMS and “C” for control,).

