### Outcome measures

The primary outcome of this study is to test whether CBT provided by a mental health professional, working in a multidisciplinary team with a dietician and a physical therapist (a three-component intervention), is effective to decrease weight compared to usual care (control) at the end of the treatment. Secondary outcomes include: reproductive, drop-out, quality of life, healthy diet, physical activity, metabolic and endocrine improvements, the health of the (unborn) child. All outcome variables are measured at the start of the study, and again at 3 months, 6 months, 9 months and 12 months. All outcome measures are displayed in Table 6. Below we give more details about the collection of the secondary outcomes.

**Table 6 Tab6:** Outcomes measures (T0, T1, T2, T3, T4)

Primary outcome	
Weight in kilograms	
Secondary outcomes	
(1) reproductive outcomes:	a) cycle duration and frequency
	b) spontaneous pregnancies
2) anthropomorphometric outcomes:	a) BMI
	b) waist circumference (WC)
	c) hip circumference (HC)
	d)WC/HC ratio
(3) clinical and biochemical PCOS features:	a) hair growth pattern
	- Ferriman Gallwey score
	b) blood pressure
	c) transvaginal ultrasound outcomes
	- ovarian volume
	- follicle count
	- total follicles per ovary
	d) endocrine outcomes
	- insulin resistance
	- hyperandrogenism
	- dyslipidemia
(4) psychological outcomes:	a) eating behaviour and disturbances
	- The Dutch Eating Behaviour Questionnaire (NVE)
	- Eating Disorder Examination Questionnaire (EDE-Q)
	b) quality of Life
	- Short Form 36 (SF-36)
	- Polycystic Ovary Syndrome Questionnaire (PCOSQ)
	c) depression
	- Beck Depression Inventory (BDI)
	d) self-esteem
	- Rosenberg Self Esteem Scale (RSE)
	e) fear of negative appearance
	- Fear of Negative Appearance Evaluation Scale (FNAES)
	f) satisfaction
	- Self-constructed questionnaire
(5) physical activity:	a) perceived level of daily physical activity
	- the International Physical Activity Questionnaire (IPAQ)
	b) the intervention group: submaximal bicycle test
(5) physical activity:	a) food intake
	-energy (calories)
	- protein
	- fat
	- saturated fat
	- carbohydrates
	- mono- and disaccharides
	- drinks (ml)
(7) other:	- attendance at meetings
	**-** drop-out and reasons for drop-out

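### The mixed model leaves the arms free to differ at baseline despite randomisation: valid, but it gives up some precision (about 5% of variance at the documented correlation of 0.90)

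*Protocol article*

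**What the plan says.** The Statistical analyses section applies one model to every outcome, with a treatment main effect, linear, quadratic and log-time terms "and all treatment-time interactions as fixed effects". Non-significant fixed effects are then removed by Wald tests, "respecting that interaction effects must be nested under their main effects". Results are expressed relative to baseline: "Effect sizes will be calculated by dividing the differences between time-point and baseline estimations and the estimated baseline standard deviation". No baseline covariate and no common baseline mean is mentioned.

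Three other places bear on this:

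- Outcome measures makes baseline the first of five outcome measurements: "All outcome variables are measured at the start of the study, and again at 3 months, 6 months, 9 months and 12 months".
- Randomisation places allocation after that first measurement: "At the baseline, after the initial assessment, participants are randomized at a 2:1 ratio".
- Sample size calculation gives the only correlation in the article, in a paragraph about interim BMI data: "We observed an intercorrelation of about 0.90 between all measurements".

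**The concern.** When baseline is an outcome row and the model has a free treatment main effect, that main effect is the fitted difference between arms at baseline (with the time terms at zero there). Each later treatment-time contrast is measured from it and so estimates a difference in raw change. Because allocation follows the baseline assessment, the true difference in baseline means is zero by design. The model spends information estimating a known quantity and passes that estimate's sampling error into every later contrast.

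The nesting rule removes the way out. A model with treatment-time terms but no treatment main effect, which is what gives the arms a common baseline, is not allowed under the reduction procedure as written. What is at stake is the width of the confidence intervals, for weight and for the long list of secondary outcomes in Table 6. Validity is not at stake.

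**Working it through.** **Inputs from the article.** r = 0.90 between measurements (interim BMI); five visits at 0, 3, 6, 9 and 12 months; 84 + 42 = 126 complete cases. **Assumed here.** Equal SD s at baseline and 12 months (the interim SDs, 6.8 and 6.6 in controls and 4.8 and 5.1 in the intervention group, are close); r of 0.7, 0.5 and 0.3 for secondary outcomes, since none is given.

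**The plan's own figures.** The article gives no figure for the precision of this contrast. Its inflation for drop-out reproduces: 126/(1 − 0.40) = 210. So does its effect size: 0.52 − 0.10 = 0.42. The 126 comes from a cited method that is not shown, and nothing below depends on it.

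**Variance of the 12-month contrast**, with categorical time and complete data, where k = 1/84 + 1/42:

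- free baseline (change score): 2s²(1 − r)k
- common baseline mean: s²(1 − r²)k
- ratio, common to free: (1 − r²)/[2(1 − r)] = (1 + r)/2

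At r = 0.90 the two factors are 0.190 and 0.200, ratio 0.95. The square root is 0.975, so the standard error is about 2.5% lower.

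| r | Source | Variance ratio | Reduction in SE | Power, if 80% with a free baseline (two-sided 5%) |
|---|---|---|---|---|
| 0.90 | article, BMI | 0.95 | 2.5% | 82.0% |
| 0.7 | assumed | 0.85 | 7.8% | 86.0% |
| 0.5 | assumed | 0.75 | 13.4% | 89.9% |
| 0.3 | assumed | 0.65 | 19.4% | 93.5% |

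**Check with the planned time curve.** Generalised least squares for 84 + 42 women, five visits, equal correlation between visits, and linear, quadratic and log(months + 1) terms gives ratios of 0.949, 0.846, 0.744 and 0.641. The shift by 1 inside the logarithm is an assumption, needed because baseline is month 0. The closed form is a close approximation for the planned model.

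**If correlation decayed over visits.** With adjacent visits at 0.90 and first-order autoregressive decay, the baseline-to-12-month correlation would be 0.90⁴ = 0.656 and the ratio (1 + 0.656)/2 = 0.828. The article, however, reports about 0.90 for all pairs, so 0.95 is the figure it supports.

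**Effect on the estimate, using the interim BMI means.** Change contrast: (31.3 − 33.8) − (32.6 − 33.3) = −2.5 + 0.7 = −1.80. Adjusted contrast with an assumed slope of 0.90: (31.3 − 32.6) − 0.90 × (33.8 − 33.3) = −1.30 − 0.45 = −1.75. The shift is 0.05 kg/m², about 3% of the difference.

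**The case against.** The strongest reply is that nothing here is wrong. Group, time and group-by-time terms with baseline among the outcomes are a standard and valid analysis of a randomised trial. For the primary comparison the loss is 2.5% of a standard error. A plain change-score formula with the stated inputs (difference 0.42, r = 0.90, two-sided alpha 0.025, power 0.90, 2:1) needs 22 + 44 = 66 completers against the 126 planned, so no primary conclusion is likely to turn on it. All of that stands, and it is why the point is rated low. It does not make the point mere preference: the change uses data already collected and has essentially no downside.

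Three stronger readings should be resisted.

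- A reader might infer that the planned analysis is biased. Under randomisation it is not.
- A reader might infer a large loss for questionnaires, hormones and diet. The article gives no correlation for any of them and no power target for them; the lower values above are assumptions. Equally, it does not support carrying 0.90 over to them.
- A reader might take the interim baseline means of 33.8 and 33.3 as chance imbalance entering the result. They describe interim complete cases in a trial with 40% observed drop-out, so they do not isolate imbalance at randomisation, and the estimate moves by only 0.05 kg/m².

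**Conclusion.** The point holds as an efficiency finding of low severity. The model as written lets the arms differ at baseline, and its reduction rule prevents a common baseline whenever an interaction is retained. Measured against a common-baseline model, the documented cost is about 5% of the variance of the 12-month contrast. This assumes that weight, the primary outcome in Table 6, behaves like BMI, for which the 0.90 was reported. For the secondary outcomes the cost is unknown: 15% to 35% of variance if the correlation lies between 0.7 and 0.3, and less if it is higher. The closed form is exact for complete data, categorical time and known covariance, and close to exact for the planned time terms.

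**What to change.** For all continuous outcomes compared between arms:

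- Keep the planned linear, quadratic and log-time terms, coded so that each is zero at baseline (for the logarithm, a shift such as log(months + 1)).
- Keep the treatment-time interactions and omit the treatment main effect, so that the arms share one baseline mean.
- State in the reduction step that this omission is exempt from the nesting rule.

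Prefer this constrained form to entering baseline as a covariate. The two are not equivalent when follow-up is missing, and the covariate form drops women who have a baseline value only, which matters with 40% drop-out.

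For SMS versus no SMS, first reconcile the Randomisation section, which assigns all three groups at baseline, with the section on the SMS maintenance intervention, which places that assignment at 3 months. If assignment is at 3 months, the 3-month value also precedes it, and the 3-month mean should be common to those two arms as well.

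The cost is a rewrite of the model statement, the time coding and the reduction rule. No new data are needed, and planned effect sizes relative to baseline can still be computed.
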